## Abstract

**Introduction:**

This study aims to evaluate the effectiveness and feasibility of the implementation of an Asthma Integrated Care Pathway (AICP) to improve care and reduce variability according to recommended clinical practice guidelines, for children presenting with acute asthma episodes in paediatric primary care, and hospital services including emergency departments.

**Methods and analysis:**

A cluster quasi-experimental implementation trial with a matched control group will be launched in a regional healthcare service. All the paediatric healthcare professionals providing care in two health districts (HDs) will receive interventions over two 12-month periods during which components of the implementation strategy to favour adoption of the AICP will be deployed cumulatively. A selected set of professionals from the same levels of care in the other HDs (*N* = 11) will serve as the comparison group. The target population of the AICP is children between 2 and 14 years old presenting with an acute asthma episode during the study period. A mixed methods evaluation guided by the RE-AIM framework will assess the effectiveness of the AICP after 12, 24, and 36 months in a set of pre-specified care and implementation outcomes at the professional level. The perceived feasibility of the AICP and its implementation from the perspective of physicians and the experience and satisfaction of patients concerning the clinical care received will be assessed through discussion groups.

**Discussion:**

This study performed in real-world settings will contribute in extending knowledge in asthma care pathways beyond emergency settings into primary care and across the healthcare continuum. In addition, its findings aim to guide health systems in reducing variability in care, increasing guideline adherence, and ultimately improving paediatric asthma outcomes across the system.

**Clinical trial registration:**

ClinicalTrials.gov, identifier [NCT06437444].

## Introduction

1

Asthma is the most common chronic disease in childhood, with a prevalence of up to 20%, depending on the geographical area (1–3). Poor disease control can lead to substandard quality of life, missed days at school, missed workdays for caregivers, visits to paediatric emergency departments (PEDs), and hospital admissions. Around 20% of children with asthma experience asthma attacks (AAs) (also called asthma exacerbations) that require medical attention, both in primary care (PC) and PEDs (4–6). Up to a 15% of patients require hospital admission (6, 7), and it is estimated that they account for around 5% of PED visits. AAs account for more than 80% of the direct costs associated with asthma (7–10). Numerous clinical practice guidelines (CPGs) have been developed with recommendations to mitigate the impact of AAs (11–14). However, difficulties in adhering to these recommendations have been reported in both PEDs and PC services (15–18).

Integrated care pathways (ICPs) aim to translate CPG recommendations into clinical processes of care within the unique culture and environment of a healthcare institution, to reduce variation, improve quality of care, and optimize outcomes for specific patient groups (19–21). In line with this, it appears that asthma care pathways have the potential to improve the management of asthma in children, as they seem to have positive results in achieving better adherence to recommended care, resulting in more efficient and homogeneous care. More specifically, it has been demonstrated that paediatric asthma care pathways implemented in PED settings could help to improve the quality of care (22) by increasing the use and timely administration of recommended medications (bronchodilators and systemic corticosteroids) (23–25), decreasing length of PED stays (25–28), decreasing risk of hospital admission (23), and increasing training in asthma management (24). Nonetheless, all asthma care pathways reported have been implemented in only one specific context, mainly in PEDs and hospital care. This limited scope, together with the recent experience of our research group with the successful implementation and scaling up of a care pathway for the management of acute bronchiolitis (29), has led us to develop a new integrated care pathway for the management of AAs at all levels of care. To this end, when designing our implementation strategy, we have also taken into account the potential barriers detected in previously implemented asthma pathways both in PC (30) and hospital care [27], such as lack of awareness of the care pathway, lack of integration of the pathway into clinic flow, or difficulty in modifying EHR or in obtaining consensus on practice changes.

The general objective of this study protocol is to evaluate the effectiveness and feasibility of the implementation of the Asthma Integrated Care Pathway (AICP) to improve the care provided to children presenting acute asthma episodes and to reduce the variability among PC and PED professionals and care settings in accordance with clinical practice guideline recommendations (11–14).

The specific objectives will be:

### Effectiveness objectives

1.1

To evaluate the effectiveness of the implementation of the AICP on: (a) increasing the rate of administration of bronchodilators using a metered-dose inhaler (MDI) with a spacer chamber in children diagnosed with a mild-to-moderate AAs in PC, PEDs, and hospital wards; (b) increasing the Pulmonary Score documentation rate at all levels of care; (c) increasing the rate of recording asthma symptoms using the Pediatric Asthma Control Tool (PACT) (31) in PC and PEDs; and (d) increasing the rate of initiation of background treatment in children with persistent asthma symptoms, in PC and PEDs.

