### Clinical intervention

2.5

The AICP is a structured multidisciplinary care plan that details the essential evidence-based steps in the care of patients with mild-to-moderate AAs and the coordinated practice of the agents involved as dictated by the evidence. In addition, the pathway determines the target population (inclusion/exclusion criteria); the sequence of common best practices during the patient's navigation through the system, according to the best available evidence in terms of: diagnostic methods and criteria, as well as their coding and recording; the provision of care and recommended clinical practices (actions, responsibilities, etc.); the educational activities for the patient and their relatives; the management of the patient and the patient's care; complex situations, management of difficulties and referral criteria; due attention to transitions between care levels and communication between professionals; and the outcomes to be pursued, evaluated and monitored.

In essence, the four core components of evidence-based clinical practice related to acute asthma as stated in the AICP (see Supplementary File S2) are:
•Assessment and recording of the Pulmonary Score;•Assessment and recording of asthma symptoms using the PACT;•Administration of background treatment in cases of persistent asthma symptoms;•Administration of bronchodilators using an MDI with a spacer chamber in children diagnosed with a mild-to-moderate asthma attack.The AICP was built on the model followed in the design of the Integrated Acute Bronchiolitis Care Pathway (29). It was developed based on the consensus of professionals involved in caring for children with asthma at different levels of care and the advice of experts in quality and medical documentation. Work started in 2020 and after an external evaluation process, its first version was approved in April 2021 (under editorial review).

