### Evaluating the effectiveness of the AICP

2.8

The main effectiveness outcome will be the change from baseline to 12 and 24 months in the rates of mild-to-moderate AA episodes seen in PC and the PED in which patients are administered bronchodilators using a MDI with a spacer chamber. We will assess the overall effect of the AICP by testing the interaction between intervention and time of measurement. Should this intervention-by-time interaction be significant (with *p* < 0.05 as the threshold for significance), planned comparisons will be performed to determine whether changes in the AICP group between baseline and each of the follow-up points are significantly different from those observed in the control group. Secondary effectiveness outcomes will be the change from baseline to 12 and 24 months after the implementation of the AICP in: (a) rate of recording of Pulmonary Score at all levels of care; (b) rate of recording of asthma symptoms using the PACT at all levels of care; and lastly, (c) the change in rate of persistent asthma symptoms in children who initiate a background treatment at all levels of care.

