#### IMPLEMENTATION

2.9.3

The degree of fidelity with which the professionals/centres have implemented the AICP and its components for the management of AAs compared to what was planned will be evaluated. For this purpose, a complete record and subsequent description will be made of the implementation process, and any adaptations made to the AICP or its components. In addition, the fidelity of the implementation strategies designed to facilitate the adoption of the AICP by professionals/centres will be evaluated. To this end, we will provide a complete record and subsequent description of each strategy's execution process and documentation of adaptations made. Further, to assess dose, quality of delivery, professionals’ responsiveness, and programme differentiation (33), the exposure of professionals/centres/centres to the strategies will be measured by a questionnaire developed ad-hoc for this project.

In addition, a representative sample of professionals from the different levels of care involved (PC, PEDs, hospital wards, PICU, and paediatric pulmonology department) with high and low adoption and implementation rates of the good practice criteria established by the AICP (administration of bronchodilator with a spacer chamber; assessment and recording of the Pulmonary Score; and assessment and recording of persistent symptoms - asthma severity) will participate in a structured process using a qualitative methodology (discussion groups) focused on identifying the main barriers and facilitators for the provision of recommended clinical practice. A purposive sample of paediatricians will be recruited stratified by level of care seeking to ensure that all views are represented. All discussion groups will count with at least 6 professionals organized by level of care. Since one of the objectives is for the professionals to express their group perception of the implementation of the AICP at their level of care, we seek to achieve intra-group homogeneity and therefore the possibility of mixing people from different levels of care in the same group is not contemplated. Sampling will continue until saturation is reached, defined as two consecutive discussion groups in which no new additional information is gathered.

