### Data management plan

2.10

This study will be carried out in accordance with international standards for the conduct of epidemiological studies, included in the International Guidelines for Ethical Review of Epidemiological Studies (37). In order to learn about the management of AAs, data will be collected from the health centres and the PED and inpatient care-paediatric pulmonology reference centres of the two HDs. This is a prospective intervention study, where the data will be collected from the EHR, using the data exploitation program of our regional health service (OSABIDE Global). The Primary Care Research Unit of Bizkaia is formally authorized by the Healthcare Directorate of Osakidetza to extract and use data from the EHR for research purposes. A diagnostic search will be carried out for the term asthma with AAs (International Classification of Diseases code J45.901). Data will also be gathered on the number of prescriptions given for inhaled bronchodilators, or inhaled and systemic corticosteroids, the recording of severity using the Pulmonary Score, and the use of a spacer chamber in mild-to-moderate attacks. In the case of prescriptions, only those made using the Basque Health Service prescription platform and associated with AA episodes will be recorded. As this data collection and recording will be performed without naming and without any participation of the patients as it is mainly routine clinical practice data, need for consent was waived by the ethics committee. Conversely, participants in the structured focus group meetings (both professionals and patients’ relatives/caregivers) will be informed about the study and their written informed consent will be obtained concerning the information directly collected from them (see Supplementary Files S5, S6).

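### The background-treatment rate is conditioned on persistent symptoms, a status whose recording the pathway aims to raise in one group only, so its intervention-by-time contrast is open to selection bias in either direction

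*Protocol article*

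**What the plan says.** Section 1.1 (Effectiveness objectives) gives objective (d) as "increasing the rate of initiation of background treatment in children with persistent asthma symptoms, in PC and PEDs". The numerator is treatment starts and the denominator is children whose symptoms are persistent.

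Section 2.8 states what appears to be the same outcome differently, as "the change in rate of persistent asthma symptoms in children who initiate a background treatment at all levels of care". There, children starting treatment form the denominator, persistence moves to the numerator, and the setting widens from primary care (PC) and paediatric emergency departments (PEDs) to every level of care.

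The PACT is the only instrument named for asthma symptoms. Its use is a secondary outcome in 2.8, "rate of recording of asthma symptoms using the PACT at all levels of care", and one of the four core components in 2.5, "Assessment and recording of asthma symptoms using the PACT". Another core component makes treatment conditional on persistence: "Administration of background treatment in cases of persistent asthma symptoms". Section 2.9.3 lists "assessment and recording of persistent symptoms - asthma severity" among the good practice criteria, which treats persistence as something the professional assesses and records.

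Section 2.6 supports recording with tools in the electronic record, training courses and monthly audit and feedback. Under 2.4 the comparison professionals receive none of this. Section 2.11 tests the effect through an intervention-by-time interaction.

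**The concern.** A between-group comparison of change is interpretable when the rule that puts an episode in the denominator works alike in both groups and all periods. Here that rule rests on persistent status, and the pathway acts on how often that status is established and written down. Three kinds of child with persistent symptoms show the problem, if persistence is read from the PACT:

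- PACT recorded, treatment started: counts 1/1.
- PACT recorded, treatment not started: counts 0/1.
- No PACT, whether treated or not: not counted.

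As recording rises in the intervention group, children move from the third kind into the first two. If those arriving differ in severity or likelihood of treatment from those already counted, the rate moves without any change in prescribing. Matching on baseline characteristics cannot remove this, because the change in selection arises after baseline. Adjusting for the baseline rate does not help either, because that rate is itself measured in a selected subset.

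At stake is the conclusion on one secondary outcome. A real gain could show as a fall, or an apparent gain could be an artefact of recording.

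**Working it through.** **The plan's own figures.** There is none to reproduce. The only power figure (80%, section 2.11) concerns the primary spacer outcome. No PACT recording rate, persistent share or background-treatment rate is given, so everything below except the episode counts is an assumption.

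**1. Selection tied to planned treatment.** Let p be the true initiation rate among children with persistent symptoms. Let k be how many times as likely a PACT is when treatment will be started as when it will not.

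Measured rate = pk / (pk + 1 − p). With p = 0.40:

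| k | Calculation | Measured rate |
|---|---|---|
| 0.5 | 0.20 / (0.20 + 0.60) | 25.0% |
| 1 | 0.40 / (0.40 + 0.60) | 40.0% |
| 2 | 0.80 / (0.80 + 0.60) | 57.1% |
| 4 | 1.60 / (1.60 + 0.60) | 72.7% |

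If k is 2 to 4 at baseline and 1 once recording is unselective, the rate drops by 57.1 − 40 = 17.1 to 72.7 − 40 = 32.7 points with no change in care. A true rise to 50% would still show as a fall of 7.1 to 22.7 points. If k starts at 0.5, the same shift gives a spurious rise of 15 points. If k is 1 throughout, there is no bias.

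**2. Selection tied to severity.** Assume one third of children with persistent symptoms are more severe (80% treated) and two thirds milder (30% treated). The true rate is (1/3)(0.80) + (2/3)(0.30) = 46.7%.

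- Recording 10% in severe and 2% in milder cases: 0.0307 / 0.0467 = 65.7%.
- Recording 70% and 60%, prescribing unchanged: 0.3067 / 0.6333 = 48.4%.
- Recording 70% and 60%, treatment improved to 85% and 40% (true rate 55.0%): 0.3583 / 0.6333 = 56.6%.

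The measured rate falls from 65.7% to 56.6% while the true rate rises from 46.7% to 55.0%. With equal recording in both strata it stays at 46.7%.

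**3. Size of the baseline denominator.** Evaluable episodes = yearly episodes × persistent share × recording rate, with an assumed share of 30%. Yearly counts are for the intervention districts: 1,100 in PC (2.11) and about 3,000 in the PED (2.2).

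| PACT recording (assumed) | PC, 1,100 | PED, 3,000 |
|---|---|---|
| 2% | 6.6 | 18 |
| 10% | 33 | 90 |
| 30% | 99 | 270 |

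Section 2.2 puts PC at around 2,000 episodes, which would give 12 to 60 at 2–10% recording. Before clustering, at a rate of 50%, the 95% half-width is 1.96 × √(0.25/n): about ±17 points at n = 33 and ±10 points at n = 99. The models for PC and emergency departments are separate (2.11), so each rests on its own column.

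**4. The 2.8(c) wording.** It needs persistent status too. If a missing PACT counts as not persistent, the rate rises mechanically with recording. If such children are excluded, the same kind of selection applies. Choosing that wording does not remove the problem.

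**The case against.** **Is the PACT the only source?** A reader might infer that persistence is known only where a PACT was recorded. The protocol does not say so. The data list in 2.10, which includes "the recording of severity using the Pulmonary Score, and the use of a spacer chamber in mild-to-moderate attacks", names no other source, but it omits the PACT as well, so it is not exhaustive and its silence proves little. The full protocol or the pathway document may define persistence in another way. This stands: sole reliance on the PACT is an inference. Even so, the protocol presents assessing and recording persistence as something the pathway promotes, so the concern does not depend wholly on the PACT.

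**Is the denominator almost empty at baseline and in controls?** A reader might infer this too. No figure supports it. Section 2.9.2 says baseline levels were considered but reports none, and a count based on PC alone leaves out the PED. The denominator is small only if recording is a few percent.

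**Must the rate fall?** No. The direction follows from the assumed selection, and the same arithmetic gives a rise under the opposite assumption.

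**Would an all-episode rate answer the question?** Not alone. It would count starts in children without persistent symptoms as success, so it cannot replace the conditional rate.

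**Would readers see the shift?** PACT recording is reported, so they would see that it changed. That does not tell them how far the treatment rate was distorted.

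**Conclusion.** The concern holds as a design weakness in one secondary outcome. Followed as written in 1.1(d), or in the inverted form of 2.8(c), the intervention-by-time contrast for background treatment is exposed to selection that differs between groups after baseline, and the stated matching and baseline adjustment do not protect against it.

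This rests on two conditions: that persistent status depends, at least in large part, on recording that the pathway promotes (a reasonable inference, not a stated fact), and that recording depends on severity or planned treatment. If the second fails, there is no bias. Under the illustrative assumptions the distortion is 17 to 33 points, enough to reverse the sign of a true 10-point gain. Those figures show what is possible; they are not estimates for this trial. The primary outcome and its power statement are unaffected. The change should be made, but the trial's main conclusion does not depend on it.

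**What to change.** In section 2.8:

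1. Reconcile 2.8(c) with objective 1.1(d), which differ in numerator, denominator and setting, and state one definition.
2. Add to the intervention-by-time models for PC and the PED the proportion of all eligible asthma-attack episodes with background treatment started, in both groups and all periods, whether or not a PACT was recorded. Base the between-group conclusion about background treatment on this rate.
3. Keep the rate among children with recorded persistent symptoms as the measure of guideline-concordant care. Report it beside the PACT recording rate by group and period, and do not interpret it alone as an intervention effect.

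The cost is a wording change and one further proportion per model. The numerator is the one 1.1(d) already needs, and section 2.10 already provides for prescription data.

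The downside is dilution. In the severity illustration, with 30% persistent and starts only in those children, a true rise from 46.7% to 55.0% becomes 0.30 × 46.7% = 14.0% to 0.30 × 55.0% = 16.5%, so 8.3 points shrink to 2.5. The all-episode rate also counts starts in children without persistent symptoms, so the two rates must be read together.

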### Implementation objectives

1.2

(a). To assess the reach of the AICP among the population eligible to receive it 12 months after its implementation; determine the extent to which the exposed population is representative of the target population; and ascertain the perception and experience of exposed users (family members) regarding the quality of care received for the management of AAs and the response to their concerns and needs (REACH)(b). To assess the degree of adoption of the AICP by professionals/centres 12 months after its implementation; and determine the degree of representativeness of adopting professionals/centres and the main barriers or difficulties for adoption (ADOPTION)(c). To assess the degree of implementation of the AICP components, their fidelity to the protocols, and any adaptations made; describe the set of actions or strategies necessary for its adequate implementation and the level of exposure of the implementing agents to them; and assess the feasibility and acceptability perceived by professionals regarding the implementation of the pathway, with special emphasis on the identification of barriers, facilitators, and strategies needed to inform future system-wide scaling up (IMPLEMENTATION)(d). To assess the sustainability of AICP implementation in the long term (24 months), resources, and adaptations required (MAINTENANCE).

## Methods and analysis

2

### Design and timeline of the study

2.1

A cluster quasi-experimental implementation trial with matched control group evaluated with mixed methods will be conducted in paediatric services of Basque Health Service, Osakidetza. The present study do not imply prospective recruitment of patients as it consists in a study performed under real world circumstances of clinical practice regarding acute asthma management by professionals of participating paediatric services. A two 12-month implementation periods will take place between May 2023 and May 2025, during which components of the implementation strategy to favour adoption of the AICP will be cumulatively deployed. This will involve, first, a set of strategies facilitating initial uptake (from 7 May 2023 to 7 May 2024); and second, a set of strategies related to broad dissemination and communication among professionals and healthcare centres involved (from 7 May 2024 to 7 May 2025) (see Supplementary File S1 for more detailed specification). The quantitative evaluation to assess the results of the implementation of the AICP at professional and patient levels will be carried out considering the year prior to the first implementation period as the baseline measurement, and three post-intervention measurements at 12, 24 and 36 months from initial implementation of the pathway until May 2026. A flow diagram with further description of the study phases is presented in Figure 1. Final quantitative results of study are expected in June 2026. The qualitative evaluation will be carried out upon the completion of the second implementation period through a structured process with discussion groups. These groups will be focused, on the one hand, on the identification of the main barriers and facilitators for the provision of recommended clinical practice by the healthcare professionals, and on the other, on patients’ (and their relatives’) experience and satisfaction with the clinical care received.

